### Adverse events

4.6

Any adverse events during the intervention period will be reported, such as bleeding, fainting, pain, infection or other severe events will be recorded with details such as the date of occurrence, degree and causality with the acupuncture treatment. If the situation worsens, the patients will be discontinued from the study and will be sent for further treatment.

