### Study design

2.1

This is a randomized controlled, paralleled neuroimaging study, with patients, assessors and data statisticians blinded to the group assignment. A total of 60 patients with SWD and 30 healthy subjects will be recruited from October 2019 to December 2020 at Beijing Anding Hospital of Capital Medical University. They were divided into a control group, a true acupoints treatment group (TATG) and a sham acupoints treatment group (SATG) by the ratio of 1:1:1. The TATG and SATG will receive 8 sessions of acupuncture treatment in 4 weeks (2 sessions every week) by a trained acupuncture operator. Cognitive function scales and MRI scanning will be performed before and after 4-week acupuncture treatment. Meanwhile, the needle sensation will be evaluated by assessment scale after each session. The control group will receive no intervention.

The study procedures are detailed in Figure 1.

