### Sample size

2.6

When calculating the sample size during the acupuncture-neuroimaging study, the number in published literature and previous studies is often considered. On the one hand, in fMRI studies, millions of voxels are used to estimate the blood oxygen level dependent (BOLD) signal indirectly, and conventional power calculations often make no sense. On the other hand, the number of participants is often constrained by scanning time and costs. In hence, considering the published acupuncture-neuroimaging literature focusing on sleep disorder, the sample size range of 16 to 32 cases show enough statistical power for brain functional analysis.^[21]^ In the present study, we plan to recruit 60 patients with SWD and 30 healthy subjects with regular sleep.

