### Randomization and blinding

2.7

Randomization will be carried out in 2 steps. Firstly, according to the inclusion exclusion criteria, the 90 participants will be divided into experimental group and control group by the ratio of 2:1; secondly, the patient with SWD will be divided into TATG and SATG according to the computer-generated random sequence using Excel's rand function (1:1 ratio). The code will be sealed in opaque envelopes and opened by researchers not involved in the recruitment following informed consent procedures and baseline testing, with direct responsibility for treatment allocation. The researchers and acupuncturists will know the allocation. Meanwhile, the participants, outcome assessors and data analysts will be blinded.

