### Sham acupuncture group

3.2

Patients in sham acupuncture group will receive 4-week manual acupuncture treatments at 10 sham acupoints (SA). According to the previous literature on setting locations of SA,^[22]^ the SA should be set aside with 1 inch beside the true point as the sham acupoint. In hence, the deqi experience of the participants in SATG will not be overemphasized. In spite of the locations of acupoints, the treatment procedures and course will be the same with TATG.

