#### Neuroimaging outcomes

4.2.2

The neuroimaging outcomes will be acquired after the MRI scanning and analysis, mainly including functional connectivity (FC) within and between resting-state brain networks. FC will be taken as the primary outcome and effect indicator, which is an optimal parameter to reflect the functional connections within and between resting-state brain networks. Numerous studies revealed changes of the brain's intrinsic functional connectivity stemming from cognitive impairments on patients with sleep disorder.^[23,24]^ In hence, FC could reflect whether specific brain regions or resting-state brain networks are involved in improvements of cognitive functions after 4-week acupuncture treatments.

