#### Resting-state fMRI data preprocessing

5.2.1

The fMRI data were preprocessed with Data Processing Assistant for Resting-Sate fMRI (DPARSF) software (http://rfmri.org/DPARSF). The first 10 volumes were discarded to allow the adaption of the subjects and the stabilization of the magnetization. The remaining volumes were slice-timing corrected for different acquisition in slice times and realigned to the first volume for head-motion correction. Based on the head motion data, the subjects were excluded according to the criteria of maximum translation as 1.5 mm and rotational parameters as 1.5 degrees in any direction. After that, the image data will be under the spatial normalization based on MNI space and resampled to 3 × 3 × 3 mm^3^. Finally, the data will be smoothed with a Gaussian kernel of 6 × 6 × 6 mm^3^ full width at half-maximum. Then, the data were temporally band-pass filtered (0.01–0.08 Hz) to reduce the low-frequency drift and high-frequency physiological noise.

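### Section 4.6 takes patients with a worsening adverse event out of the study, not only off acupuncture, so as written their week-4 outcomes are lost

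*Protocol article*

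**What the plan says.** Section 4.6 begins: "Any adverse events during the intervention period will be reported". It gives bleeding, fainting, pain and infection as examples, and asks for the date, the degree and the causal relation to acupuncture to be recorded. It then says: "If the situation worsens, the patients will be discontinued from the study and will be sent for further treatment".

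On timing, section 2.1 says: "Cognitive function scales and MRI scanning will be performed before and after 4-week acupuncture treatment". Section 4.3 gives the same two time points for RBANS and ANT. On the primary outcome, section 4.2.2 says: "FC will be taken as the primary outcome and effect indicator".

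Section 2.7 separates patients from healthy controls by eligibility. Only the patients are then randomised, 1:1, to true (TATG) or sham (SATG) acupoints, and the envelopes are opened after baseline testing. Section 2.6 says: "we plan to recruit 60 patients with SWD and 30 healthy subjects with regular sleep". Section 5.1 compares the groups by one-way ANOVA and then two at a time, and section 5.2.2 also uses one-way ANOVA. Neither names an analysis population.

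**The concern.** Stopping a treatment and leaving a trial are different things. A patient can stop needling on clinical grounds and still attend the final scan and tests. Section 4.6 names only the second, and nothing elsewhere in the article keeps such a patient for assessment.

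This matters for three reasons. First, the rule acts after randomisation, and its trigger may be related to the treatment: the same section asks whether each event was caused by acupuncture. Second, there is only one post-baseline measurement of connectivity and cognition, so a patient removed during the course has a baseline value and nothing after it. Third, the healthy controls are not randomised, so the comparison of TATG with SATG alone carries the causal claim. Removing patients for treatment-related reasons makes that comparison one between selected subsets.

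**Working it through.** **Step 1. What happens to a removed patient.** Following the sections in time order:

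| Stage | Source | Patient removed mid-course |
|---|---|---|
| Baseline tests and first MRI | 2.7, 3.1, 4.3 | Measured |
| Randomisation to TATG or SATG | 2.7 | Done |
| 8 sessions in 4 weeks | 2.1 | Partly received |
| Adverse event worsens | 4.6 | Leaves the study |
| MRI, RBANS and ANT after week 4 | 2.1, 4.3 | Not obtained, if 4.6 is followed literally |

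The loss of the week-4 values follows from putting these sections together; no section states it outright. The text of section 4.4 gives no time point for the PSQI, so the argument does not rely on it.

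**Step 2. The plan's own figure.** The planned numbers are consistent: 90 split 2:1 gives 60 and 30, and 60 split 1:1 gives 30 and 30. Section 2.6 bases them on precedent (16 to 32 cases). It gives no effect size, SD, power or dropout rate, so there is no power figure to reproduce.

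**Step 3. Illustrative shift in one arm's mean.** Let k of 30 patients be removed, and let the removed patients' mean differ from the retained patients' mean by D (in SD). With f = k/30, the mean of all randomised patients is (1 − f) × m + f × (m − D) = m − fD, where m is the retained mean. Analysing only the retained patients therefore shifts the arm mean by fD = (k/30) × D. Both k and D are assumptions.

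| k removed from one arm | D = 0.5 SD | D = 1.0 SD |
|---|---|---|
| 1 | 1 × 0.5/30 = 0.017 | 1 × 1.0/30 = 0.033 |
| 2 | 0.033 | 0.067 |
| 3 | 0.050 | 0.100 |
| 4 | 2.0/30 = 0.067 | 4.0/30 = 0.133 |

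**Step 4. From arm mean to contrast.** The shift in TATG minus SATG is the difference of the two arm shifts. With D = 1.0 in both arms and 3 removed from one and 2 from the other, it is 0.100 − 0.067 = 0.033 SD. With equal numbers and equal D it is zero. The values in step 3 apply to the contrast only if all losses fall in one arm.

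**Step 5. Would the rule be used at all?** The chance of at least one removal among 60 is 1 − (1 − p)^60. For assumed rates p of 1%, 2%, 5% and 10% this is 45%, 70%, 95% and over 99%, with 0.6, 1.2, 3 and 6 removals expected.

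**Step 6. Precision.** For a two-sided 5% test of two means, the difference detectable with 80% power is (1.960 + 0.842) × √(2/n) SD: 0.72 at n = 30 per arm, 0.75 at 28 and 0.76 at 27. At an assumed difference of 0.74 SD, power is 82% at 30 per arm, 79% at 28 and 78% at 27, with equal losses in both arms. The cost in power is a few percentage points.

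**The case against.** The strongest reply is that this is one sentence in the safety paragraph of a condensed article. It does not say that assessments are withheld, and the full protocol may provide for follow-up. That is fair as far as it goes: the loss is read from the wording. But the wording refers to the study, and a statistical analysis plan cannot supply a scan that was never taken. If the full protocol does keep these patients, the article's sentence misstates it and still needs correcting.

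A reader might go further in four ways that the document does not support.

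- **That the trial abandons intention-to-treat.** No such analysis set is declared, so there is none to abandon. An unnamed analysis set may properly sit in the analysis plan.
- **That acupuncture will look better tolerated.** Section 4.6 has events reported and recorded with their degree and causality. A patient who then leaves already has her event on record.
- **That losses will be greater in the true arm.** Needling there continues until deqi, while section 3.2 says of the sham arm that "the deqi experience of the participants in SATG will not be overemphasized". Yet that section goes on to say that, apart from location, procedures and course are the same. Section 2.7 also says that researchers and acupuncturists know the allocation. An imbalance is possible but not shown.
- **That acupuncture will look more effective.** The primary outcome is connectivity, for which the article gives no better or worse direction. Nothing in it ties a complication such as bleeding or infection to week-4 connectivity or cognition.

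Section 5.2.1 also removes people for head motion ("the subjects were excluded according to the criteria of maximum translation as 1.5 mm"), and section 2.2 allows voluntary withdrawal. These too can leave the randomised set incomplete, but they are separate matters and do not show that section 4.6 is wrong.

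**Conclusion.** The point holds in a limited form. Section 4.6 merges stopping treatment with leaving the study. Applied as written, it removes randomised patients before the only post-baseline scan and cognitive tests, and so leaves the TATG versus SATG comparison incomplete for a reason that may be related to treatment. The direction of any bias is unknown.

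Its size is also unknown, because the article gives no event rate. Under the assumptions of 1 to 4 removals, all from one arm, and a difference of 0.5 to 1.0 SD, an arm mean moves by about 0.02 to 0.13 SD. The contrast moves less if losses are balanced. If worsening events are rare, the effect is small. The case for changing the text is that the loss is imposed by the protocol, is avoidable, and cannot be repaired at analysis.

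**What to change.** Leave the clinical decision about treatment as it is and change only the data rule.

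- **Section 4.6:** state that a patient who stops acupuncture because of an adverse event stays in the study and is invited to the scheduled week-4 cognitive tests, the PSQI and, where safe, the MRI, unless she withdraws consent.
- **Section 5:** state that TATG and SATG are compared by assigned arm in all randomised patients with week-4 data, and that discontinuations are reported by arm with reasons.

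The cost is two sentences and a small number of assessments already in the schedule for every patient. There are two drawbacks. Some patients will decline to return, so the loss is reduced but not removed. The estimate will also include patients who received only part of the course, so it describes the effect of assignment to acupuncture and not of completing it.

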### Quality control, data collection and management

4.7

A series of training sessions will be held before the beginning of this study, which ensuring all researches get fully understood the standard procedures of this study. The medical imaging technicians will monitor the qualities of neuroimaging data after every scanning. The clinical and cognitive function data are required to be recorded on printed Case Report Forms (CRF) at each visit point. The completed CRFs will be undergone the double-entry verification in EpiData Entry software to ensure the accuracy of the data. All the MRI data will be stored in discs after finishing every scanning. After the data entry and verification as required, the CRF should be kept in the order of number, and filled with the search catalogue for reference. All original files shall be kept within the time limit specified.

## Statistical analysis

5

### Clinical data analysis

5.1

The measurement data of each visit in different groups will be described by means of mean ± standard deviation. Clinical data including scores of cognitive function assessments from the 3 groups will be compared using one-way ANOVA, and further statistical analysis will be conducted between 2 groups.

The counting data of each visit in different treatment groups were described by frequency (composition ratio). χ^2^ test or nonparametric test were used for the changes of the 3 groups before and after treatment.

### Neuroimaging data preprocessing and analysis

5.2

#### Resting-state fMRI data preprocessing

5.2.1

The fMRI data were preprocessed with Data Processing Assistant for Resting-Sate fMRI (DPARSF) software (http://rfmri.org/DPARSF). The first 10 volumes were discarded to allow the adaption of the subjects and the stabilization of the magnetization. The remaining volumes were slice-timing corrected for different acquisition in slice times and realigned to the first volume for head-motion correction. Based on the head motion data, the subjects were excluded according to the criteria of maximum translation as 1.5 mm and rotational parameters as 1.5 degrees in any direction. After that, the image data will be under the spatial normalization based on MNI space and resampled to 3 × 3 × 3 mm^3^. Finally, the data will be smoothed with a Gaussian kernel of 6 × 6 × 6 mm^3^ full width at half-maximum. Then, the data were temporally band-pass filtered (0.01–0.08 Hz) to reduce the low-frequency drift and high-frequency physiological noise.

#### Functional connectivity analysis

5.2.2

Independent component analysis was applied to extract the resting-state brain networks by GIFT software (University of New Mexico, Albuquerque, NM). The number of independent components in all data was calculated by method of the minimum description length (MDL) technique. 30 components were estimated. Randlnit and Bootstrap operations were applied to evaluate the independent components. According to research objectives, independent components were selected based on the largest spatial correlation comparing with previous resting-state brain network templates. Then, resting-state brain networks were calculated by the way of goodness of-fit after removing the components not related to the spectrum of resting-state networks. The best goodness-of-fit score of components were normalized to *Z*-scores with Fisher's *r*-to-*z* transformation to acquire the entire brain *Z*-score map of each subject. Then we extracted time series of each network component to calculate the Pearson correlation coefficient (*r*) of each network component and other network time series, namely functional network connectivity (FNC). The resulting r values were normalized into *Z* values by Fisher-*Z* transformation. For group-level analyses, the functional connectivity of Intra-network and inter-network was performed by one-way ANOVA using SPM12 software (*P < *.05, corrected by false discovery rate (FDR) for multiple comparisons). Finally, BrainNet Viewer was used to display the result onto a 3D brain surface.

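### The only group-level test stated for the primary outcome is a one-way ANOVA with no true-versus-sham contrast, so a significant result could come from the non-randomised healthy group alone

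*Protocol article*

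**What the plan says.** Section 4.2.2 sets the primary outcome: "FC will be taken as the primary outcome and effect indicator". Section 5.2.2 gives its group-level test: "the functional connectivity of Intra-network and inter-network was performed by one-way ANOVA using SPM12 software", at P < .05, "corrected by false discovery rate (FDR) for multiple comparisons". It does not list the groups, name a contrast, add a pairwise step, or say whether week-4 values or changes from baseline are analysed.

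For the clinical and cognitive scores, section 5.1 says "Clinical data including scores of cognitive function assessments from the 3 groups will be compared using one-way ANOVA" and then "further statistical analysis will be conducted between 2 groups". The pair, the method and any multiplicity rule are not given.

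On the groups, section 2.1 says "They were divided into a control group, a true acupoints treatment group (TATG) and a sham acupoints treatment group (SATG) by the ratio of 1:1:1". Section 2.7 describes randomisation in two steps. In the first, "according to the inclusion exclusion criteria, the 90 participants will be divided into experimental group and control group by the ratio of 2:1". In the second, only the patients with shift work disorder (SWD) are allocated to TATG or SATG, by a computer-generated sequence. The control group is healthy and untreated (sections 2.1, 2.4 and 3).

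Section 4.2.2 and the Discussion both cite studies in which connectivity changes with sleep disorder. The Discussion also says that the sham arm is there to remove the placebo effect.

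**The concern.** The trial asks whether needling true points does more than needling sham points. Only the TATG-SATG comparison answers that, and only that comparison is protected by randomisation. The first step in section 2.7 sorts people by eligibility into patients and healthy volunteers. Nothing is left to chance there, although it is listed as a randomisation step.

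A three-group F test rejects when any group differs from the others. If healthy volunteers differ from patients, it can reject while the true and sham arms are identical. The protocol gives reason to expect such a difference and names no further step for FC that would show where a significant result comes from. At stake is a significant primary result being reported as an effect of acupuncture when it reflects having SWD or not. FDR correction does not help with this, because it controls error across connections and does not say which groups differ.

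**Working it through.** **The plan's own figure.** The stated size is 60 patients and 30 healthy subjects, so 90 / 3 = 30 per group. Section 2.6 takes this from a published range of 16 to 32 cases and gives no effect size, SD or power. No formula can reproduce it; one can only note that 30 lies inside the range.

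**Inputs.** From the document: three groups, n = 30 each, alpha 0.05, one-way ANOVA. Assumed, because the document gives no figure: a patient-healthy gap d of 0.2 to 1.0 SD. Also assumed: one connection, week-4 values, no FDR.

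**Omnibus test when true equals sham.** Put the group means, in SD units, at (d, 0, 0) for healthy, true and sham. The grand mean is d/3, and the sum of squared deviations is (2d/3)² + 2(d/3)² = (2/3)d². The noncentrality is 30 × (2/3)d² = 20d². The critical value of F on 2 and 87 degrees of freedom is 3.10. Power comes from the noncentral F distribution.

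| Assumed gap d (SD) | Noncentrality 20d² | Three-group F significant | Direct true-versus-sham test significant |
|---|---|---|---|
| 0.2 | 0.8 | 11% | 5% |
| 0.3 | 1.8 | 20% | 5% |
| 0.5 | 5.0 | 49% | 5% |
| 0.8 | 12.8 | 89% | 5% |
| 1.0 | 20.0 | 98% | 5% |

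**What the significant F tests contain.** In 40,000 simulated trials with true equal to sham, 91% of the significant F tests at a gap of 0.5 SD, and 94% at 0.8 SD, came with no significant true-sham difference.

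**The pairwise step in section 5.1.** In the same simulations, requiring a significant F and then a significant TATG-SATG test gives a false true-versus-sham claim in 0.491 × 0.089 = 4.4% of trials at a gap of 0.5 SD, and in 0.892 × 0.0557 = 5.0% at 0.8 SD. That is about the nominal level.

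**The direct contrast.** A two-sided t test at 0.05 with 30 per arm, without baseline adjustment, has power 21%, 48% and 86% for true-sham differences of 0.3, 0.5 and 0.8 SD. It reaches 80% power at 0.74 SD.

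**The case against.** The strongest reply is that section 5.2.2 is condensed. It does not say in words that three groups enter the ANOVA, at which time, or on levels or change. Post-hoc contrasts may stand in an analysis plan that is not shown. This stands in part: the document does not prove that the omnibus F is the sole efficacy test. But three groups is the natural reading, since section 5.1 applies the same test to all three and a two-group ANOVA would simply be a t test. The document does fix a test for the primary outcome, and that test does not target the randomised comparison.

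Four stronger readings are tempting and are not supported:

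- **That the null hypothesis is bound to be false.** This needs a comparison of levels, which section 5.2.2 does not state. On change scores a stable patient-healthy gap cancels. The cited studies also give no size and do not imply a difference in every connection.
- **That the cognitive outcomes have the same fault.** Section 5.1 adds a pairwise step, and with TATG-SATG tested after the F the false-claim rate is about 4% to 5%. What is missing there is the name of the pair that decides efficacy.
- **That the F test costs power.** It does if healthy controls lie midway between true and sham: 38% against 48% at 0.5 SD. That is an unusual configuration. If true acupuncture brings patients to the healthy level, the figures are 49% against 48%.
- **That a false picture of normalisation is common.** At a gap of 0.8 SD with no acupuncture effect, exactly one arm differs from healthy, after a significant F, in about 12% of trials. By symmetry only about 6% would favour true acupuncture. No section proposes reading results this way.

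**Conclusion.** The point holds for the primary outcome. As written, section 5.2.2 can give a significant FC result that says nothing about true versus sham acupuncture, because the non-randomised healthy group enters the test and no randomised contrast is named.

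The size depends on a gap that the document does not give: from 11% at 0.2 SD to 98% at 1.0 SD, against 5% for the direct test. These figures are for one outcome on week-4 values before FDR. They show how far the test can miss the question and are not error rates of the planned FDR-corrected analysis. If change is analysed the problem is smaller but need not vanish: the healthy group is untreated and not randomised, so regression to the mean and non-specific effects of treatment can still separate it from the patients.

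For the cognitive scores only a matter of naming remains. The healthy group itself is not a mistake; it is useful as a reference.

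**What to change.** - **Section 5.2.2:** make the efficacy test of FC one pre-stated TATG-versus-SATG contrast in the 60 randomised patients, using the week-4 value adjusted for the baseline value, with FDR across connections. Keep the healthy group for a separate baseline comparison (60 SWD versus 30 healthy) and as a descriptive reference after treatment.
- **Section 5.1:** name TATG versus SATG as the efficacy comparison among the pairwise tests already planned.
- **Sections 2.1 and 2.7:** describe the healthy group as a non-randomised reference group, and confine the word randomisation to the TATG-SATG allocation.

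The cost is wording and a different model and contrast in the analysis. Scans before and after treatment are already planned for the patients, so no new data are needed.
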